### Consent, screening and registration

Written informed consent will be obtained prior to the commencement of all trial assessments, tests and procedures by authorised members of the trial team. Screening investigations will be conducted to confirm eligibility following consent and prior to registration. These investigations will include: CT neck, chest, abdomen and pelvis (without iodinated contrast); echocardiogram/multiple gated acquisition (MUGA); single 12-lead electrocardiogram (ECG); vital signs; ophthalmology examinations (best corrected visual acuity; intraocular pressure and slit lamp fundoscopy); full blood count (FBC); urea and electrolytes (U&Es); liver function tests (LFTs) and thyroid function tests (TFTs); serum pregnancy test for premenopausal women. Eligible patients will then be registered to the trial centrally via the University of Leeds automated 24 h system. Whenever possible, a biopsy of an identified iodine refractory lesion will be obtained following registration; archival tissue from initial thyroidectomy will also be requested.

### Treatment and assessment schedules

Quality of life will be assessed within 28 days of registration for all participants, and tissue samples will be collected within the same timeframe where applicable. Participants will be asked to observe a low iodine diet from two weeks prior to receiving a baseline I-123 SPECT/CT scan which must be completed within 28 days of registration; 0.9 mg recombinant human TSH (rhTSH) will be given via intramuscular administration two days and one day prior to administration of I-123. Prior to day one of treatment participants will have further assessments including repeat blood tests.

Participants will then be treated with 75 mg of oral Selumetinib twice daily for four weeks; doses will be taken approximately 12 h apart. Repeat assessments including haematology and biochemistry will be conducted on day 14 and day 28; where applicable blood samples for cell-free DNA assessment will also be collected. An I-123 SPECT/CT scan at the end of treatment, day 28 (±1 day), will be reviewed centrally. The increase in uptake will be deemed significant if there is presence of any clinically relevant, targeted uptake in a lesion in which there was previously no uptake or there is an increase of 30% or more in uptake in a lesion with evidence of some uptake on the baseline scan. Participants will be asked to recommence the low iodine diet two weeks prior to the post treatment scan and will again be administered 0.9 mg rhTSH two days and one day prior to the scan. Participants will continue to observe the low iodine diet and take Selumetinib whilst the post treatment scan is undergoing review (for a maximum of 18 days). A further two to three SPECT/CT scans will also be acquired and used to predict the radiation dose that may be achieved with radioiodine treatment.

Participants not deemed to have sufficient increase in iodine uptake will cease treatment with Selumetinib, can return to a usual diet and will continue to be followed up for safety purposes until 30 days after completion of Selumetinib treatment. These individuals will receive no further trial treatment.

Participants with sufficient increase of iodine uptake will go on to receive treatment with I-131 and will continue to take Selumetinib until two days after administration of I-131 (if applicable) when the low iodine diet can be discontinued. rhTSH 0.9 mg will be administered two days and one day prior to I-131 therapy. An activity of 5.5 GBq (±10%) I-131 sodium iodide will be administered orally. In the absence of any strong evidence of benefit from a dosimetric approach, it is felt reasonable to stick to empirical activities as per current standard UK practice. However, following I-131 therapy, dosimetry calculations will be made from three to four SPECT/CT scans. A standardised calibration protocol will be used by sites to optimise and standardise SPECT/CT image data across participants. Therefore an essential element of the this trial is the need to set up, for the first time, a network of UK centres able to perform quantitative I-123 and high activity I-131 imaging.

For participants consenting to blood sample collection for PBI analysis, samples will be collected 24 and 144 h post I-131 therapy.

Upon completion of I-131 therapy, participants will be followed up quarterly for the first 12 months and then 6 monthly for the duration of the trial (i.e. until the last patient recruited reaches 12 months follow up) or until evidence of disease progression is confirmed by CT scan. Follow-up assessments will include measurement of thyroglobulin and antithyroglobulin antibodies; thyroid function test; CT neck, thorax, abdomen and pelvis. Quality of life assessments will be repeated at each follow up for the first 12 months, and where applicable blood sample collection for cell-free DNA assessment will occur at three months and six months.

For all participants, TSH suppression to less than 0.1 units should be maintained throughout treatment and follow-up. Also, for all participants (including those not receiving I-131 therapy), assessments at 30 days post end of Selumetinib treatment will include vital signs, 12-lead ECG, haematology, echocardiogram and repeat quality of life measures.

The participant pathway can be seen schematically in Fig. 1, and Table 2 (SPIRIT diagram) details the assessment schedule.

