**Fig. 1 Fig1:**
[figure not shown]
Participant pathway

**Table 2 Tab2:** Minimum schedule of assessments (SPIRIT diagram)

	Baseline		Treatment				End of Treatment	Follow Up
	Within 14 days prior to registration	Within 28 days of registration	Selumetinib			I-131 Therapy	30 days post end of Selumetinib treatment	3 monthly for first 12 months then 6 monthly for duration of trial^b^
			Day 1	Day 14	Day 28			
Informed consent	X							
Patient details (initials, date of birth, sex)	X							
Medical History	X							
Physical Examination/Vital signs	X		X	X	X		X	X
Ophthalmologic assessment	X							
12-Lead ECG	X		X				X	
Laboratory tests	X		X	X	X		X	X
Pregnancy test	X		X			X	X	X^c^
Echocardiography /MUGA	X		X					
Dispensing of Selumetinib			X					
Tissue collection		X						
CT neck, thorax, abdomen and pelvis	X^a^							X
I-123 SPECT/CT		X			X			
SPECT/CT for Lesion Dosimetry post I-131 therapy						X		
Adverse Events	X		X	X	X	X	X	X^d^
Concomitant Medications	X		X	X	X		X	
Quality of life (QLQ-C30, QLQ-H&N35 and EQ-5D™)		X					X	X^e^
Protein bound iodine blood sample collection						X^f^		
Cell-free DNA blood sample collection			X	X	X		X	X^g^

^a^if CT scans have not been performed within 28 days of starting treatment, an additional CT neck, chest, abdomen, and pelvis must be performed to enable assessment of response and progression-free survival as per RECIST criteria

^b^Participants who do not proceed to radioiodine therapy will be followed up for safety purposes until 30 days after completion of Selumetinib treatment only

^c^Pregnancy test to be done at the first and second 3 monthly follow up visits (3 month and 6 month follow-up)

^d^Adverse reactions only at follow up visits

^e^Quality of life is assessed at baseline, end of treatment and 3 monthly for the first 12 months of follow-up

^f^Collected 24 and 144 h following I-131 dosing

^g^3 and 6 months only

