#### Secondary endpoints

Safety: Serious adverse events (SAEs) from registration until 30 days post cessation of trial therapy (Selumetinib or I-131 therapy); suspected unexpected serious adverse reactions (SUSARs) and serious adverse reaction (SARs) recorded for all from start of protocol treatment for the lifetime of the trial;Toxicity: Adverse reactions (ARs) as graded by common terminology criteria for adverse events (CTCAE) v4.0;Overall survival (OS): calculated from date of registration to date of death; censoring will occur at last known date alive for those alive at time of analysis;Sufficient iodine uptake: reviewed centrally; sufficient uptake is defined as presence of any clinically relevant uptake in a lesion in which there was previously no uptake or an increase of 30% or more in uptake in a lesion with evidence of some uptake on the baseline scan;Radiological response: assessed via CT scans and based on response evaluation criteria in solid tumours (RECIST) v1.1.

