### Analysis

Statistical analysis for final and interim analyses are fully detailed in separate analysis plans. The full analysis set will include all registered participants receiving at least one dose of Selumetinib and will be equivalent to the safety analysis set. The iodine uptake (IU) cohort will include participants from the full analysis set who were deemed to have sufficient I-123 uptake following treatment with Selumetinib. All other participants in the full analysis set will be the non-IU cohort. All efficacy endpoint analyses will be conducted on the IU cohort only, unless otherwise specified in the analysis plan. Safety analyses will be conducted on the safety analysis set with data summarised for each study cohort and overall during initial therapy.

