#### Secondary endpoint analyses

SAEs, SARs and SUSARs will be reported overall and by treatment period (Selumetinib, I-131) for all participants and for the IU and non-IU cohorts.

The number and proportion of participants experiencing each grade of toxicity will be summarised in the same analysis sets.

OS will be summarised using Kaplan-Meier curves; OS at 12 months and median OS will both be presented alongside CIs.

The proportion of participants with sufficient iodine uptake to progress to I-131 will be presented with corresponding 95% CI. This will also be presented excluding individuals who did not receive Selumetinib for seven days prior to the scan.

The proportion of participants in the IU cohort achieving at least a partial response will be presented with 95% CIs. The proportion of participants in each best response category (complete response, partial response, stable disease, and progressive disease) will also be presented.

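### The stated follow-up stops at CT-confirmed progression and no later vital-status collection is described, so overall survival, if run as written, would be informatively censored and probably overstated

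*Protocol article*

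**What the plan says.** **Follow-up.** Under Treatment and assessment schedules, participants who complete I-131 are seen quarterly for a year, "then 6 monthly for the duration of the trial (i.e. until the last patient recruited reaches 12 months follow up", with the alternative end point "or until evidence of disease progression is confirmed by CT scan". In Table 2 the follow-up column reads "3 monthly for first 12 months then 6 monthly for duration of trial". The table has no survival-status row and no contact labelled as post-progression.

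**Endpoint.** Secondary endpoints defines OS as "calculated from date of registration to date of death; censoring will occur at last known date alive for those alive at time of analysis". Secondary endpoint analyses adds Kaplan-Meier curves and says that "OS at 12 months and median OS will both be presented alongside CIs". OS is part of a secondary objective, and the exploratory analyses relate lesional absorbed dose to it.

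**Population.** The Analysis section states that "All efficacy endpoint analyses will be conducted on the IU cohort only", unless the analysis plan specifies otherwise.

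**Other reporting channels.** Serious adverse events are collected until 30 days after trial therapy ends. Only serious adverse reactions and SUSARs are recorded throughout the trial, and follow-up visits record adverse reactions only (Table 2, note d). A later death from thyroid cancer fits none of these.

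**The concern.** OS needs vital status up to death or the data cut-off, but the only follow-up rule given ends at progression. With nothing further collected, the last date on which a progressed participant is known to be alive falls at or near the progression scan. Kaplan-Meier treats people censored on that date as having the same future risk of death as those still followed. Progression normally signals a higher risk, so the censoring is informative.

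The 12-month and median OS would then mainly reflect deaths without prior progression, and the exploratory analysis of absorbed dose against OS would inherit the problem. An analysis plan cannot recover deaths that were never collected. For that reason this is more than a detail left out of a condensed article: the article states a stopping point that does not fit an endpoint it also states.

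**Working it through.** **1. The trial's own PFS figures (Sample size).** A median of 6 months with exponential survival gives 12-month PFS of 0.5^(12/6) = 25%, as stated. The alternative of 44% implies a hazard ratio of ln(0.44)/ln(0.25) = 0.592, consistent with the stated 0.6. Both figures reproduce.

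**2. How many participants are affected.** PFS events by 12 months: 1 − 0.44 = 56% under the alternative and 1 − 0.25 = 75% under the null. Of 38 IU participants that is 0.56 × 38 = 21.3 and 0.75 × 38 = 28.5. Those whose event is progression rather than death leave scheduled follow-up before the 12-month OS time point.

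**3. Model for the size.** The article gives no death rates, so these inputs are assumptions:
- share f of PFS events that are deaths without progression: 5%, 10% or 20%;
- median survival m after progression: 9, 12, 18, 24 or 36 months;
- constant hazards.

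Let λ = −ln(PFS at 12 months)/12, d = fλ (death without progression), p = (1 − f)λ (progression) and μ = ln 2/m (death after progression).
- True OS(t) = exp(−λt) + p[exp(−μt) − exp(−λt)]/(λ − μ).
- Kaplan-Meier OS with every progressor censored exactly at progression tends to exp(−dt).

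**4. Central case, PFS 44%, f = 10%, m = 18 months.** λ = 0.82098/12 = 0.06842, d = 0.00684, p = 0.06157, μ = 0.03851.
- True OS(12) = 0.440 + 0.06157 × (0.630 − 0.440)/0.02991 = 0.831.
- Censored at progression: exp(−0.0821) = 0.921.

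**5. Range at 12 months.**

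| 12-month PFS | Case | True OS | Censored at progression | Difference (points) |
|---|---|---|---|---|
| 44% | central (10%, 18 months) | 83.1% | 92.1% | +9.0 |
| 44% | largest gap (5%, 9 months) | 76.6% | 96.0% | +19.4 |
| 44% | smallest gap (20%, 36 months) | 83.4% | 84.9% | +1.5 |
| 25% | central (10%, 18 months) | 76.3% | 87.1% | +10.8 |
| 25% | largest gap (5%, 9 months) | 66.9% | 93.3% | +26.4 |
| 25% | reversed (20%, 36 months) | 77.2% | 75.8% | −1.4 |

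OS is overstated in 29 of the 30 combinations. In the exception, the assumed death hazard after progression (0.0193 per month) is below the one before it (0.0231). At 24 months the central gap is wider: 61.2% true against 84.9% at PFS 44%, and 51.4% against 75.8% at PFS 25%. This matters for median OS.

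**6. Progression found only at visits.** A simulation with n = 38 censored each progressor at the next 3-monthly visit, counted from registration for simplicity, so that deaths before that visit still count. The central case becomes 83.1% against 89.1% at PFS 44% (6.0 points) and 76.3% against 83.3% at PFS 25% (7.0 points). On average about 20 and 13 of the 38 remain under observation at 12 months.

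**The case against.** The strongest reply is that the article does not censor OS at progression. Its rule is "censoring will occur at last known date alive for those alive at time of analysis", which presupposes that somebody knows who is alive at analysis. PFS has its own, different censoring date, so the authors keep the two apart. The progression clause sits in a description of visits and can be read as ending scheduled CT and blood tests only. Table 2 is headed as a minimum schedule, shows no stop at progression and has no vital-status row even before progression, although PFS counts deaths. Its silence therefore says little about the later period in particular. The participant pathway figure is not shown, and the full protocol may track survival by another route.

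Much of this stands. It rules out the stronger reading, which a reader might infer, that the protocol prescribes censoring OS at progression and that reported OS will therefore be too high. The size depends wholly on assumed hazards. The direction could also reverse: if post-progression deaths reached the trial through chance reports while surviving progressors stayed censored at progression, OS would be pulled down.

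OS is also a descriptive secondary endpoint, with no test and no role in the sample size or stopping rules. With 38 participants and OS near 80%, the 95% interval half-width is already about 1.96 × √(0.8 × 0.2/38) = 12.7 points.

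What does not fall is the mismatch itself. The article gives an explicit end of follow-up, and nothing shown says how vital status is obtained afterwards.

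**Conclusion.** The point holds conditionally. The stated end of follow-up does not support the stated OS endpoint. If the trial is run as written, many of the 56% to 75% of IU participants with a PFS event by 12 months would be censored for OS at or near progression. Such censoring is informative and would probably overstate OS, provided that the risk of death is higher after progression than before it.

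The illustrative overstatement of 12-month OS at PFS 44% is about 1.5 to 19 points. A central case with 3-monthly detection gives about 6 to 7 points across the two PFS scenarios. These figures rest on assumed death rates and constant hazards, not on anything in the article. They would shrink or vanish if vital status is collected by a route not described.

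The primary PFS analysis is unaffected. Severity is moderate: OS is secondary and descriptive, but vital status not collected during the trial is hard to recover later.

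**What to change.** Reconcile Treatment and assessment schedules and Table 2 with Secondary endpoints and Secondary endpoint analyses:

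- State that scheduled visits and scans stop at confirmed progression, but that vital status and date of death are collected for all IU participants until the end of the trial, from routine records or by phone.
- State that OS is censored at the last vital-status date, checked in the same way for progressed and non-progressed participants, so that deaths are not picked up selectively.
- Add a survival-status row to Table 2.

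If the full protocol already does this, one clarifying sentence is enough. Otherwise the cost is a short amendment, one follow-up form and a few status checks per participant, with no extra scans or trial visits. The article reports that recruitment was open at submission, so a change at that stage would still protect most of the OS data.

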**Fig. 1 Fig1:**
[figure not shown]
Participant pathway

**Table 2 Tab2:** Minimum schedule of assessments (SPIRIT diagram)

	Baseline		Treatment				End of Treatment	Follow Up
	Within 14 days prior to registration	Within 28 days of registration	Selumetinib			I-131 Therapy	30 days post end of Selumetinib treatment	3 monthly for first 12 months then 6 monthly for duration of trial^b^
			Day 1	Day 14	Day 28			
Informed consent	X							
Patient details (initials, date of birth, sex)	X							
Medical History	X							
Physical Examination/Vital signs	X		X	X	X		X	X
Ophthalmologic assessment	X							
12-Lead ECG	X		X				X	
Laboratory tests	X		X	X	X		X	X
Pregnancy test	X		X			X	X	X^c^
Echocardiography /MUGA	X		X					
Dispensing of Selumetinib			X					
Tissue collection		X						
CT neck, thorax, abdomen and pelvis	X^a^							X
I-123 SPECT/CT		X			X			
SPECT/CT for Lesion Dosimetry post I-131 therapy						X		
Adverse Events	X		X	X	X	X	X	X^d^
Concomitant Medications	X		X	X	X		X	
Quality of life (QLQ-C30, QLQ-H&N35 and EQ-5D™)		X					X	X^e^
Protein bound iodine blood sample collection						X^f^		
Cell-free DNA blood sample collection			X	X	X		X	X^g^

^a^if CT scans have not been performed within 28 days of starting treatment, an additional CT neck, chest, abdomen, and pelvis must be performed to enable assessment of response and progression-free survival as per RECIST criteria

^b^Participants who do not proceed to radioiodine therapy will be followed up for safety purposes until 30 days after completion of Selumetinib treatment only

^c^Pregnancy test to be done at the first and second 3 monthly follow up visits (3 month and 6 month follow-up)

^d^Adverse reactions only at follow up visits

^e^Quality of life is assessed at baseline, end of treatment and 3 monthly for the first 12 months of follow-up

^f^Collected 24 and 144 h following I-131 dosing

^g^3 and 6 months only

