### Outcomes

#### Primary endpoint

The primary endpoint of the trial is PFS at 12 months, reported as the percentage of participants alive and progression-free at 12 months. PFS is calculated from date of registration to first documented evidence of disease progression or death. Participants who have not progressed at the time of analysis will be censored at the last date alive and progression-free.

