#### Primary endpoint analysis

The proportion of participants alive and progression free at 12 months will be presented with corresponding confidence intervals (CI). The primary analysis will test the hypothesis that PFS in the IU cohort is less than or equal to 25%, against an alternative of 44% based on the Nelson-Aalen estimate of the cumulative hazard function at 12 months, following the methodology of Case and Morgan [27].

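### The primary set is defined by iodine uptake but CT follow-up depends on receiving I-131, so a participant with uptake who misses I-131 may be censored early from 12-month PFS

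*Protocol article*

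**What the plan says.** All references are to the Protocol article.

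- **Analysis.** The IU cohort is "participants from the full analysis set who were deemed to have sufficient I-123 uptake following treatment with Selumetinib". Receipt of I-131 is not a condition. On its use: "All efficacy endpoint analyses will be conducted on the IU cohort only, unless otherwise specified in the analysis plan".
- **Primary endpoint analysis.** The test of 12-month PFS, 25% or less against 44%, is run in that cohort with the Nelson-Aalen estimate.
- **Treatment and assessment schedules.** Efficacy follow-up has one stated starting point: "Upon completion of I-131 therapy, participants will be followed up quarterly for the first 12 months". The 30-day safety follow-up is given to one group: "Participants not deemed to have sufficient increase in iodine uptake will cease treatment with Selumetinib", and these participants are then followed for safety only.
- **Table 2, footnote b** (on the follow-up column): "Participants who do not proceed to radioiodine therapy will be followed up for safety purposes until 30 days after completion of Selumetinib treatment only". The table marks CT at baseline and at the follow-up visits, and not at the visit 30 days after Selumetinib.
- **Primary endpoint.** PFS runs from registration to documented progression or death. "Participants who have not progressed at the time of analysis will be censored at the last date alive and progression-free".

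**The concern.** Membership of the primary set depends on uptake, while the data needed for the primary endpoint depend on a later step, I-131. Someone who qualifies on the scan and then does not receive I-131 falls between the two. The main text does not put that person under the 30-day rule, but footnote b does, and no passage schedules a response CT for them.

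There is room for this to happen. Between the day 28 scan and I-131 lie up to 18 further days of Selumetinib during central review, a pregnancy test at the I-131 visit, and possible adverse events. The article mentions participants who do not receive I-131, without saying whether any of them are in the IU cohort.

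If those who miss I-131 tend to have a worse outlook, their censoring is informative and the 12-month estimate is too high. A single-arm test against a fixed 25% has no control arm in which similar losses could offset this. The 10% drop-out allowance protects precision; it does not remove bias. Overall survival and response, also analysed in the IU cohort, share the gap.

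**Working it through.** **1. The plan's own figures.** A median of 6 months under exponential survival gives 0.5^(12/6) = 25% at 12 months. The hazard ratio for 44% is ln 0.44 / ln 0.25 = 0.592, which rounds to the stated 0.6. A Case and Morgan type design on the log cumulative hazard (one-sided 10%, 80% power), with an assumed accrual of 1 IU participant per month (the article gives no rate), has its optimum at N = 34 with the interim at 21. Then 34/0.9 = 37.8, which rounds up to 38. Both stated sizes, 38 and 21, are reproduced, so 34 is used as the evaluable number below.

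**2. When follow-up ends for an IU participant without I-131.** Longest stated intervals: 28 days from registration to baseline scan, 28 days of Selumetinib, 18 days of scan review, 30 days of safety follow-up. 28 + 28 + 18 + 30 = 104 days, about 3.4 months. This takes Selumetinib as starting straight after the baseline scan.

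**3. Worst case under the null.** Suppose m of 34 are lost before any event is seen and all would have failed by 12 months. The observed rate is S = 0.25 × 34/(34 − m).

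For the rejection probability, let n = 34 − m, Λ = −ln S, Λ₀ = −ln 0.25 = 1.386 and se(S) = √[(1 − S)/(S·n)]. Then P(reject) = Φ{[Λ₀ − Λ − 1.2816·se(0.25)] / se(S)}.

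| m | n | S | Λ | se(0.25) | se(S) | P(reject) |
|---|---|---|---|---|---|---|
| 0 | 34 | 25.0% | 1.386 | 0.297 | 0.297 | 0.100 |
| 2 | 32 | 26.6% | 1.326 | 0.306 | 0.294 | 0.130 |
| 3 | 31 | 27.4% | 1.294 | 0.311 | 0.292 | 0.147 |
| 4 | 30 | 28.3% | 1.261 | 0.316 | 0.290 | 0.167 |

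The same worst case at the interim, with 2 of 21 lost, gives 0.25 × 21/19 = 27.6%, above the 25% futility reference.

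**4. Less extreme assumptions.** These come from a simulation of a single-stage Nelson-Aalen test with 38 IU participants, true cohort PFS of 25%, and k participants censored at 3.5 months. The values of k and of PFS in the untreated are assumed. The test on the log scale rejects in about 0.13 with full follow-up, because of the plug-in variance and discreteness, so only the change should be read.

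| Untreated participants | Mean estimate, full follow-up | Early events seen | Early events not seen |
|---|---|---|---|
| k = 4, PFS 25% | 25.9% | 26.0% | 27.3% |
| k = 4, PFS 10% | 26.0% | 27.1% | 29.1% |
| k = 8, PFS 10% | 26.0% | 28.5% | 32.8% |

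At PFS 10%, rejection moves from about 0.13 to 0.14 (events seen) or 0.19 (not seen) for k = 4, and to 0.18 or 0.36 for k = 8.

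**5. Largest overstatement under the alternative.** If treated participants have 44% and all k untreated fail, the cohort rate is 0.44 × (38 − k)/38: 41.7% for k = 2, 39.4% for k = 4, 34.7% for k = 8. If the k are censored before any event, the estimate stays near 44%. The gap is about 2, 5 and 9 points.

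**The case against.** The strongest reply is that footnote b is shorthand. The article treats sufficient uptake and going on to I-131 as one event: it says that those with sufficient uptake will receive I-131, and it uses 38 both for participants with uptake (Sample size) and for participants treated (Design). On that reading the footnote repeats the main text. In addition, Table 2 is headed a minimum schedule, the article condenses a fuller protocol, and the efficacy rule yields to a separate analysis plan.

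Much of this stands. The gap probably comes from wording and not from intent, and the full protocol may close it. But the footnote as printed is an explicit instruction that differs from the main text, and an analysis plan cannot recover scans that sites were told not to schedule.

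A reader might infer more: that likely failures are in fact being removed, that the primary result becomes an estimate in I-131-treated participants only, or that the true type I error is 13% to 17%. The article does not support these readings. It gives no count of, or reasons for, IU participants missing I-131. In the pilot that it describes, eight participants had sufficient uptake and all eight were treated, which is a small sample but points to a low number. Documented progression or death before I-131, or during safety follow-up, still counts as an event. Untreated participants also stay in the risk set until their last progression-free date.

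**Conclusion.** The mismatch is real and rests on the text alone: the analysis set is based on uptake, CT follow-up on I-131, and footnote b is wider than the main text. An IU participant without I-131 may leave follow-up by about 3.4 months, against a 12-month endpoint, with no scheduled response CT.

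The bias is conditional. It is upward if missing I-131 is related to poor prognosis or if early progression is not imaged. It is essentially nil under the null with equal prognosis and early events seen. The 13%, 15% and 17% error rates are a worst case for 2, 3 or 4 of 34, with every one an unseen failure; the plan supplies neither assumption. The number affected may well be small. The point is worth correcting because the lost data cannot be recovered at analysis and the change is cheap.

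**What to change.** Reconcile the Treatment and assessment schedules section, Table 2 footnote b and the Analysis section:

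- Word footnote b so that it applies to the non-IU cohort only.
- State that progression and death dates are collected to month 12 for every consenting IU participant, whether or not I-131 is given. Routine-care imaging is enough.
- Keep these participants in the primary analysis.
- Add a sensitivity analysis that counts IU participants without I-131 as failures.

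The cost is a few lines of wording and some extra data collection for a few participants. The sample size of 38 and the treatment do not change. Participants who withdraw consent to follow-up will still be censored, and the sensitivity analysis shows how much that could matter.
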